## Abstract

**Introduction:**

Chronic pelvic pain (CPP) affects more than 1 million UK women with associated healthcare costs of £158 million annually. Current evidence supporting interventions when no underlying pathology is identified is very limited and treatment is frequently inadequate. Gabapentin (a GABA analogue) is efficacious and often well tolerated in other chronic pain conditions. We have completed a successful pilot randomised controlled trial Gabapentin for Pelvic Pain 1 (GaPP1) and here describe the protocol for our definitive multicentre trial to assess the efficacy of gabapentin in the management of CPP in women Gabapentin for Pelvic Pain 2 (GaPP2).

**Methods and analysis:**

We plan to perform a double-blind placebo-controlled randomised multicentre clinical trial, recruiting 300 women with CPP from up to 40 National Health Service hospitals within the UK. After randomisation, women will titrate their medication (gabapentin or placebo) over a 4-week period to a maximum of 2700 mg or placebo equivalent and will then maintain a stable dose for a 12-week period. Response to treatment will be monitored with validated questionnaires and coprimary outcome measures of average and worst pain scores will be employed. The primary objective is to test the hypothesis that treatment with gabapentin has the potential to provide an effective oral treatment to alleviate pain in women with CPP in the absence of any obvious pelvic pathology.

**Ethics and dissemination:**

Ethical approval has been obtained from the Coventry and Warwick Research Ethics Committee (REC 15/WM/0036). Data will be presented at international conferences and published in peer-reviewed journals. We will make the information obtained from the study available to the public through national bodies and charities.

**Trial registration number:**

ISRCTN77451762; Pre-results.

## Introduction

Chronic pelvic pain (CPP) affects more than 1 million women in the UK.^1–3^ It is associated with significantly reduced quality of life (QoL),^4 5^ a 45% reduction in work productivity and it has been estimated that caring for women with CPP in the UK costs £158 million annually.^6 7^ CPP can be associated with underlying pathology such as endometriosis, but in up to 55% of women no obvious cause can be identified at laparoscopy.^6^ Management of CPP is difficult when no pathology is identified, as no established gynaecological treatments are available. Due to its effectiveness in other chronic pain conditions, gabapentin (a GABA analogue), is increasingly being prescribed for CPP in both primary and secondary care.^8^ However, there is no good quality evidence in CPP specifically on which to base this practice.^9^ To our knowledge, there is only one study evaluating the use of gabapentin for CPP, which did not have a placebo arm.^10^ This small study in 56 women, compared gabapentin with amitriptyline and showed gabapentin to have greater efficacy at improving pain scores at 12 months. However, efficacy of gabapentin has been proven in other chronic pain conditions. A recent high-quality review showed the number needed to treat to be 5.8 (95% CI 4.3 to 9.0) to achieve at least 50% pain intensity reduction in painful diabetic neuropathy (829 patients); 7.5 (95% CI 5.2 to 14) to achieve at least 50% pain intensity reduction in postherpetic neuralgia (892 patients) and 5.4 (95% CI 2.9 to 31) to achieve at least 30% pain intensity reduction in fibromyalgia (150 patients).^8^ Moreover, it is a drug that is very well tolerated: all-cause withdrawal rates are similar to placebo (gabapentin: 20%; placebo: 19%; number of studies: 17; number of participants: 3063).^8^

Given the clinical need for a medical treatment for CPP with no identifiable underlying pathology and the strong evidence supporting the acceptability and efficacy of gabapentin in other chronic pain conditions, we considered that further investigation of gabapentin as a potential treatment for CPP in women was warranted. We hypothesise that treatment of women with CPP in the absence of any obvious pelvic pathology with gabapentin will alleviate pain and improve physical and emotional functioning. We initially performed a successful pilot randomised controlled trial (RCT) (GaPP1).^11 12^ Here, we describe the protocol for our definitive multicentre trial to assess the efficacy of gabapentin in the management of CPP in women (GaPP2).

### Objectives

#### Primary objective

The primary objective is to test the hypothesis that treatment with gabapentin has the potential to provide an effective oral treatment to alleviate pain in women with CPP in the absence of any obvious pelvic pathology.

#### Secondary objective

The secondary objective is to test the hypothesis that treatment with gabapentin has the potential to improve physical and emotional functioning in women with CPP in the absence of any obvious pelvic pathology.

### Outcomes

#### Primary outcome

We will employ coprimary outcome measures of average and worst pain scores recorded on a Numerical Rating Scale (NRS). To capture the cyclicity that may occur with CPP, weekly pain scores (on a 0–10 scale) will be recorded during the final 4 weeks of treatment (weeks 13–16 postrandomisation), in the form of: (1) ‘average pain this week’ and (2) ‘worst pain this week’.

The composite ‘average’ pain score will be taken as the average of the four weekly average pain scores submitted, and the composite ‘worst’ pain score as the worst of the four weekly worst pain scores submitted.

#### Secondary outcomes

Physical and emotional function and QoL.Satisfaction with treatment.Patient estimate of whether on active treatment or on placebo group, and confidence in and reasons for estimate.Adherence to trial treatments, as reported by the participants.Concomitant analgesic use, as reported by the participants.Adverse events, as reported by participants (principally those that are serious and detailed in the summary of product characteristics and those that are unexpected).General practitioner/hospital consultations, as reported by the participants.Time off work and ‘presenteeism’.

## Methods and analysis

### Study design

GaPP2 is a double-blind placebo-controlled randomised multicentre clinical trial (figure 1). We will screen women with CPP from up to 40 National Health Service hospitals within the UK. Women will return weekly NRS pain scores to the trials office for 4 weeks after initial consent. Those women meeting the inclusion criteria at the end of these 4 weeks will be randomised. We will randomise 300 women (150 to gabapentin, 150 to placebo). After randomisation and titration, participants will receive treatment with the maximum tolerated dose for 12 weeks. Participants and the healthcare team will be unblinded at the end of their treatment.

**Figure 1 F1:**
[figure not shown]
Study flow chart. AE, adverse event; NRS, Numerical Rating Scale; PROM, patient-reported outcome measure.

### Participants

A total of 300 women with a history of CPP with no obvious pelvic pathology detected at laparoscopy will be recruited to the trial.

### Inclusion criteria

Women aged between 18 and 50 years.CPP (with or without dysmenorrhoea or dyspareunia) of >3-months duration.Pain located within the true pelvis or between and below anterior iliac crests.No obvious pelvic pathology at laparoscopy (laparoscopy must have taken place at least 2 weeks ago, but no more than 36 months prior to screening).Using or willing to use effective contraception if necessary to avoid pregnancy.Able to give informed consent.For both the worst and average prerandomisation NRS questions, at least three of the four weekly scores returned to the trials office. At least two of the worst pain scores should be ≥4/10. Potential participants who have been on a stable dose of an analgesic, other than gabapentin or pregabalin, for at least 4 weeks prior to screening will be eligible.

### Exclusion criteria

Dysmenorrhoea aloneknown pelvic pathology:endometriosis (macroscopic lesions)complex or >5 cm ovarian cystfibroid >3 cmdense adhesionscurrent malignancy under treatmentcurrent use of gabapentin/pregabalintaking Gonadotrophin Releasing Hormone (GnRH) agonists and unable/unwilling to stopsurgery planned in the next 6 monthshistory of significant renal impairmentprevious allergic reaction to gabapentinbreast feedingpregnantplanning pregnancy in next 6 monthspain suspected to be of gastrointestinal origin (positive Rome III Diagnostic Criteria)coenrolment in another Clinical Trial of an Investigational Medicinal Product.

### Participant enrolment

Research nurses (dedicated or through the National Institute for Health Research’s Clinical Research Network, depending on the site) will be employed for the duration of the study to approach eligible women, provide them with patient information sheets and offer them the opportunity to discuss the trial, and obtain informed consent for screening. Consent will only be taken once the patient has had ample time to read the patient information sheet and had her questions answered.

### Study settings

We will recruit patients from gynaecology outpatient clinics, gynaecology wards and day surgery units and CPP clinics within the UK.

### Intervention and randomisation

Randomisation to gabapentin or placebo will occur once written informed consent has been obtained, final eligibility established from the pain responses provided during the screening phase and baseline questionnaires completed. The Birmingham Clinical Trials Unit (BCTU) will provide third-party web-based randomisation with telephone backup. A minimisation procedure using a computer-based algorithm will be used to avoid chance imbalances in treatment allocation and the following potentially important variables:presence or absence of dysmenorrhoea (a pain score of ≥4/10 will be considered significant);psychological distress measured by the General Health Questionnaire (GHQ) (scored as 0–12 with a cut-off of 0–1 and 2–12 for minimisation);use of sex hormonal treatments (combined oral contraceptive, progestogens, levonorgestrel-releasing intrauterine system (Mirena));centre.

A ‘random element’ will be included in the minimisation algorithm, so that each patient has a probability (unspecified here) of being randomised to the opposite treatment that they would have otherwise received. Full details of the algorithm used will be stored in a confidential document at BCTU. Both participants and the research team will remain blind to allocation.

### Dose regimen

After randomisation, participants will be allocated a trial treatment pack from the hospital pharmacy containing either gabapentin or placebo oral tablets, both of identical appearance. Participants will start on one capsule (300 mg) daily and will increase by one capsule (300 mg) increments every 3 days until they perceive that they are gaining adequate pain relief, or report side effects (eg, dizziness, somnolence, mood changes, appetite and poor concentration) that preclude them from further increases, up to a maximum dose of nine capsules (2700 mg), as shown in table 1. The titration phase will last a maximum of 4 weeks. If necessary they will be advised to titrate down to the last tolerated dose with minimal side effects. They will be asked to maintain their best tolerated dose until the end of week 16. Patients will be advised and given written instructions regarding their dosing regimen by a member of the research team. It will be recommended that the drug should be taken in three equally divided doses daily. The same protocol will be used for the placebo. When the participant stops treatment, the dose will be reduced according to a dose reduction chart and written instructions will be given. Patients will be allowed to use other medication (including analgesics, self-medication and alternative treatments, eg, acupuncture) throughout the study period.

**Table 1 T1:** Dose escalation schedule for GaPP2

Day in study	Total number of capsules/day (maximum)	Dosing	Maximum daily dose of gabapentin (mg)
1	1	One capsule night	300
2	1	One capsule night	300
3	1	One capsule night	300
4	2	One capsule two times a day	600
5	2	One capsule two times a day	600
6	2	One capsule two times a day	600
7	3	One capsule three times a day	900
8	3	One capsule three times a day	900
9	3	One capsule three times a day	900
10	4	One capsule two times+two capsules at night	1200
11	4	One capsule two times+two capsules at night	1200
12	4	One capsule two times+two capsules at night	1200
13	5	Two capsules two times+one capsule once	1500
14	5	Two capsules two times+one capsule once	1500
15	5	Two capsules two times+one capsule once	1500
16	6	Two capsules three times a day	1800
17	6	Two capsules three times a day	1800
18	6	Two capsules three times a day	1800
19	7	Two capsules two times+three capsules night	2100
20	7	Two capsules two times+three capsules night	2100
21	7	Two capsules two times+three capsules night	2100
22	8	Three capsules two times+two capsules once	2400
23	8	Three capsules two times+two capsules once	2400
24	8	Three capsules two times+two capsules once	2400
25	9	Three capsules three times a day	2700
26	9	Three capsules three times a day	2700
27	9	Three capsules three times a day	2700
28–112	Remain on maximum tolerated dose until the end of week 16 (not exceeding 2700 mg or nine capsules per day). Daily dose should be divided equally into three doses.		

GaPP2, Gabapentin for Pelvic Pain 2.

### Data collection

#### Data storage

All the data generated from the study will be stored in a bespoke database, which will be password protected. All paperwork will be kept in a locked filing cabinet in a locked office. All data will be stored in accordance with the Data Protection Act.

#### Screening

A member of the research team will assess the woman for eligibility to enter the screening phase. All data will be recorded on a case report form (CRF) and transferred to a secure database, which will trigger the start of the weekly collection of pain scores.

#### Participant log

The clinical research team will keep an anonymised electronic log of women who fulfil the eligibility criteria, women who are invited to participate in the study, women recruited and women who leave the trial early. Reasons for non-recruitment (eg, non-eligibility, refusal to participate and administrative error) will also be recorded. During the course of the study, we will document reasons for withdrawal from the study and lost to follow-up if available.

#### Pain scores

Pain NRS will be collected by an automated text messaging system. Two texts will be sent to the women’s mobile phone, asking about average and worst pain, respectively, and the woman will be asked to reply to the text message with her pain score, rating it from 0 (for no pain at all) to 10 (being worst pain imaginable). To capture cyclicity, these will be collected weekly during the eligibility phase (weeks −1 to −4) and during the last 4 weeks of the treatment phase (weeks 13–16).

#### Treatment diaries

Participants will be provided with a treatment diary at the same time as their medication pack is dispensed. The following measures will be completed by the participant daily from day 1 of treatment until week 16:dose of gabapentin takenreason for any change in trial medication dosealternative therapies usedany visits to a healthcare professional.

#### Questionnaires

A questionnaire will be given to all participants before randomisation but after screening (baseline) and at 16 weeks postrandomisation (see table 2 for full schedule of assessments). This will include the following validated tools:

**Table 2 T2:** Schedule of outcome assessments for GaPP2

Phase	Run-in				Baseline, randomisation and treatment dispensed	Titration	Treatment					End of study and unblinding	Taper
Duration (weeks)	−4 to −1				0	1–4	5–12	13–16					17–19
Weekly worst and average NRS	**x**	**x**	**x**	**x**				**x**	**x**	**x**	**x**		
SF-12					**X**							**X**	
BPI					**X**							**X**	
PCS					**X**							**X**	
SAQ					**X**							**X**	
BFI					**X**							**X**	
GHQ					**X**							**X**	
WPAIQ					**X**							**X**	
PainDETECT					**X**							**X**	
PUF					**X**								
Adverse events						**X**	**X**	**X**				**X**	**X**
Permitted/concomitant medication	**X**					**X**	**X**	**X**					**X**
Adherence or discontinuation						**X**	**X**	**X**					**X**

BFI, Brief Fatigue Inventory; BPI, Brief Pain Inventory; GHQ, General Health Questionnaire; NRS, Numerical Rating Scale; PCS, Pain Catastrophising Scale; PUF, Pelvic Pain and Urinary/Frequency Patient Symptom Scale; SAQ, Sexual Activity Questionnaire; SF-12, 12-Item Short-Form Health Survey; WPAIQ, Work and Productivity Activity Impairment Questionnaire.

12-Item Short-Form Health Survey (SF-12): a QoL measure.^13^Brief Pain Inventory (BPI)^14^: a tool to measure pain intensity and interference of pain in a patient’s life.Brief Fatigue Inventory (BFI).^15^GHQ^16^: to identify psychological distress.Work and Productivity Activity Impairment Questionnaire (WPAIQ).^17^Pain Catastrophising Scale (PCS).^18^Sexual Activity Questionnaire (SAQ).^19^PainDETECT: to identify a neuropathic component to pain.^20^Pelvic Pain and Urinary/Frequency Patient Symptom Scale (PUF) (at baseline only).

The questionnaire at baseline will include questions to capture the baseline demographic and clinical characteristics of the participants.

All questionnaires will be anonymised and completed in private.

#### Adverse events

Participants will collect information about adverse events in their treatment diaries. However, they will be instructed to contact the clinical research team at any time after consenting to join the trial if they have an event that requires hospitalisation or an event that results in persistent or significant disability or incapacity. Any serious adverse events (SAEs) that occur after joining the trial will be reported in detail in the participant’s medical notes and followed up until resolution of the event. The assessment of seriousness, causality and expectedness will be conducted assuming that the participant received gabapentin, with the blinding not broken. All SAEs will be reported to the Academic and Clinical Central Office for Research and Development (ACCORD) Research Governance (http://www.accord.ed.ac.uk) and Quality Assurance Office based at the University of Edinburgh immediately or within 24 hours. ACCORD will onward report all SAEs to BCTU within 7 days.

#### Termination of study

Participants will be unblinded at the end of the study and if taking gabapentin will have the option to continue on treatment or will be tapered off treatment. Participants who have been on placebo will be given the choice to start on gabapentin, which will be prescribed by their clinician. Participants will be given an emergency contact card to carry while participating in the study. The blinding code will only be broken in emergency situations for reasons of patient safety, where knowledge of the treatment administered is necessary for the treatment of a SAE. Participants whose randomisation codes are broken will cease treatment with the study drug, but will continue to be followed up. Participants may discontinue from the trial at any time at their own request, or they may be withdrawn at any time at the discretion of the research team for safety, behavioural or administrative reasons. Data collection is envisaged to be complete in September 2018.

### Sample size

We have based our sample size on being able to detect a minimally important difference (MID) in NRS scores with high levels of power. Studies have shown the MID in this population to be around 1 point on a 0–10 scale.^21^ Our pilot study showed worst and average pain scores to have SDs between 2.0 and 2.5. If the SD is at the lower end of these estimates, 86 patients in each group (172 in total) would be required to have 90% power (P=0.05) to detect a difference of 1 point. If the SD is at the higher end, we could detect the same difference with 80% power (P=0.05) with 100 patients in each group. We have assumed the latter SD (2.5) to be conservative. To account for any increase in the risk of type I error that may be associated with having coprimary outcome measures, we have applied a Bonferroni correction (alpha reduced to 0.025 from 0.05), which increases the sample size to 120 per group. Furthermore, to account for an expected average 20% lost to follow up, we will randomise 150 per group, 300 patients in total.

### Proposed analyses

Data analysis will be by intention to treat. Every attempt will be made to gather data on all women randomised, irrespective of compliance with the treatment protocol. Appropriate baseline characteristics, split by treatment group, will be presented for each outcome. Point estimates, 95% CIs and P values from two-sided tests will be reported.

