#### Primary analysis

We will use a linear regression model to estimate differences in worst and average NRS scores between the two treatment groups, including baseline score and the minimisation variables as covariates. The P value from the associated χ^2^ test will be produced and used to determine statistical significance. A Bonferroni correction will be applied as there are two primary outcomes. Further analysis using a repeated measures (multilevel) model will also be performed incorporating all eight recorded scores.

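### Average and worst pain are each tested at a Bonferroni alpha of 0.025, but the only interval level prescribed is 95%, so the primary intervals do not match the primary tests

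*Protocol article*

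**What the plan says.** Three places in the protocol article bear on this.

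- **Sample size.** The target difference is 1 point and the SD is 2.5 ("We have assumed the latter SD (2.5) to be conservative"). Because there are two primary outcomes, "we have applied a Bonferroni correction (alpha reduced to 0.025 from 0.05), which increases the sample size to 120 per group". At the uncorrected alpha of 0.05 the article gives 100 per group.
- **Primary analysis.** The decision rests on a test: "The P value from the associated χ^2^ test will be produced and used to determine statistical significance". The sentence that follows is "A Bonferroni correction will be applied as there are two primary outcomes".
- **Proposed analyses** (the introduction to all analyses). "Point estimates, 95% CIs and P values from two-sided tests will be reported".

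No other confidence level appears in the article, and average and worst pain are not exempted from the general one.

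**The concern.** A two-sided test at level alpha and a confidence interval at level 1 − alpha are two views of one calculation: the interval excludes zero exactly when the test is significant. A test at 0.025 therefore pairs with a 97.5% interval. The article fixes both the test level and the interval level for the primary outcomes, and the two do not pair. This is a mismatch between stated rules, not a detail left for a later document.

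At stake is how a borderline primary result is read. If P falls between 0.025 and 0.05 for average or worst pain, the report would show an interval that excludes zero beside a test that is not significant by the trial's own rule. The article does not say which of the two governs interpretation of the interval. The intervals will also be read against the 1-point minimally important difference, and the stated ones are narrower than those that go with the level used to size the trial.

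**Working it through.** **Inputs.** From Sample size: difference 1 point, SD 2.5 (2.0 at the lower end), power 80% (90% at SD 2.0), alpha 0.05 reduced to 0.025, 20% loss to follow-up. From Proposed analyses: 95% intervals, two-sided tests. The correlation between average and worst pain is not given; 0 to 0.9 is assumed below.

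**1. The plan's own sample size.** n per group = 2(z₁₋α/₂ + z₁₋β)² SD²/δ², with the t-test solution beside it.

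- SD 2.0, alpha 0.05, 90% power: 85 (t-test 85.03, so 86). Stated: 86.
- SD 2.5, alpha 0.05, 80% power: 99 (t-test 99.08, so 100). Stated: 100.
- SD 2.5, alpha 0.025, 80% power: 119 (t-test 120.08). Stated: 120.
- Loss to follow-up: 120/(1 − 0.20) = 150. Stated: 150.

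The figures reproduce, which confirms that 0.025 per outcome is the operative test level.

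**2. Interval width.** The multiplier is 1.960 for a 95% interval and 2.241 for a 97.5% interval; 2.241/1.960 = 1.144, so the matching interval is about 14% wider. At SD 2.5 and 120 per group, without covariate adjustment, SE = 2.5 × √(2/120) = 0.323.

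- 95% half-width: 1.960 × 0.323 = 0.63 points.
- 97.5% half-width: 2.241 × 0.323 = 0.72 points.

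On these figures, test and interval disagree when the observed difference lies between about 0.63 and 0.72 points in either direction.

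**3. How often they disagree, per outcome.**

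- No true effect: 0.05 − 0.025 = 2.5%.
- True difference 1 point, SD 2.5, 120 per group: power is 87.3% at alpha 0.05 and 80.4% at alpha 0.025. Unrounded, 0.8725 − 0.8043 = 0.068, or about 6.8%.

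**4. The two outcomes together.** With a bivariate normal pair and critical value c, the chance that at least one exceeds c in absolute value is 1 − P(|Z₁| < c, |Z₂| < c). At correlation 0 this is 1 − 0.975² = 4.94% for the planned tests and 1 − 0.95² = 9.75% for the pair of 95% intervals.

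| Assumed correlation | Planned tests (0.025 each): family error | Pair of 95% intervals: at least one misses its true value |
|---|---|---|
| 0 | 4.94% | 9.75% |
| 0.5 | 4.65% | 9.07% |
| 0.7 | 4.30% | 8.35% |
| 0.8 | 4.02% | 7.81% |
| 0.9 | 3.62% | 7.04% |

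The middle column is the error of the decision rule that the article states. The right-hand column is a coverage property of the reported intervals, whatever the true effects. Under no effect it is also the chance that at least one 95% interval excludes zero. With 97.5% intervals, the joint miss rate would be that of the middle column.

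**The case against.** The strongest reply is that nothing is wrong with the error control. A reader might infer from the 95% intervals that the trial runs a family error of 8% to 10%, or that the correction has been undone. The article does not support that. Significance is to be decided by the Bonferroni-corrected P value, and nowhere is an interval used to declare success. The larger error would arise only if someone replaced the stated rule with one based on the 95% intervals. This part of the reply stands in full.

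A second reply is that the reporting sentence is general and the Bonferroni sentence specific, so the latter may already cover the primary intervals. That is possible but not what the text supports. The Bonferroni sentence comes directly after the one on the P value and does not mention intervals, and 95% is the only level given anywhere.

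A third reply is that interval levels are the kind of detail an article leaves to the full protocol or analysis plan. That would answer a complaint that the level is missing. Here a level is stated, and it does not fit the stated test.

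A fourth reply is that a 95% interval is a valid estimate for one outcome and may reasonably stand beside an adjusted test. This is true, and it is one reason why the point is minor. But the article does not say that the intervals are unadjusted. Nor would meta-analysis be harmed: a standard error can be recovered from an interval of any stated level.

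**Conclusion.** The point holds as a minor reporting inconsistency. The primary tests run at 0.025 each and the prescribed intervals at 95%, so the two can disagree when 0.025 < P < 0.05: 2.5% per outcome under no effect, and about 6.8% at a true 1-point difference. The 6.8% and the half-widths assume SD 2.5, 120 analysed per group and no gain from covariate adjustment. The 14% difference in width is a ratio of normal multipliers and does not depend on the SD or the sample size.

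The joint miss rate of about 7% to 10% for the two 95% intervals depends on the assumed correlation. Both scores come from the same women over the same four weeks, so the higher correlations, and with them the lower end of that range, are plausible. It should not be quoted as the trial's type I error, which the planned rule keeps at or below 5%. The sample size is unaffected.

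**What to change.** Amend the reporting sentence under Proposed analyses so that it prescribes 97.5% confidence intervals for the two primary outcomes (composite average and composite worst NRS score) and 95% intervals for all other outcomes. Interval and test then agree for every possible result, whether the Bonferroni correction is made by a 0.025 threshold or by doubling the P value.

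The cost is one sentence and primary intervals about 14% wider (half-width about 0.72 instead of 0.63 points on the planning assumptions). No extra participants are needed.

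If the trial team prefers to keep 95% throughout, the lesser alternative is to label the primary intervals as unadjusted for multiplicity and to state that inference rests on the corrected P value. Either choice should be fixed before unblinded results are seen, so that a borderline result does not decide which statistic is emphasised.
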